### Safety Analysis

Incidence rates of AE/SAE, including symptomatic hyponatremia and plasma sodium overcorrection during index hospitalization, will be calculated at study end as described for the primary outcome. Summary statistics of multiple occurrences of AE/SAE within individual patients, will be presented separately. An independent data safety monitoring board will oversee the trial and conduct a safety-analysis after 1,000 patients have completed the 30-day follow-up.

### Subgroup Analyses

We are interested in whether the treatment effect, i.e., the difference between the two treatment arms, on the primary outcome and its components varies between the following patient subgroups: sex (female and male), age (<70 and ≥ 70 years), severity of hyponatremia (mild-moderate: 120–130 mmol/l and severe: <120 mmol/l), underlying disease (stroke, heart failure, SIAD, hepatic impairment, chronic kidney disease, malignancy, surgical diagnosis) as well as the main treatment used (fluid restriction, diuretics, infusion, urea, vaptans). To this end, we will fit logistic regression models, including treatment arm, subgroup and the interaction term as explanatory variables. Significance for interaction is defined by α = 5%. If a significant interaction effect results, the treatment effect will be calculated for the respective outcome and subgroups separately.

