#### B. Control Group (Standard Care)

##### 1. Diagnosis

Laboratory analysis (blood and urine samples) to diagnose hyponatremia will be at the discretion of the attending physician according to local standards of care. The final hyponatremia diagnosis will be made by the study team at discharge according to all available clinical and laboratory information as well as treatment response.

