### Sample Size Calculations and Statistical Analyses

#### Determination of Sample Size

Sample size was estimated based on our already completed observational multi-center study in 298 patients with profound hyponatremia (37, 38). The study showed a 30-day mortality rate of 6.4% and a 30-day rehospitalization rate of 18.5%. Of the re-hospitalized patients, ~2% died and thus were counted twice. We therefore propose a combined event rate of 23% under standard care. Our systematic review identified only one study that investigated the impact of targeted correction of hyponatremia on mortality and rehospitalization (25). In this observational study, an absolute reduction of the combined event rate of 7.1% (33.7 vs. 26.6%) was reported. Through our intervention, we expect to achieve an absolute risk reduction for mortality and rehospitalization of 5 %. Sample size was calculated for a Pearson's χ^2^-test. We set 80% power for a two- sided test with an α error of 5%. A drop-out rate of 10% was assumed. In order to have 2050 evaluable patients, 2,278 patients must be recruited.

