#### Secondary Analysis

Each of the components of the primary outcome, death and rehospitalization, will be analyzed separately as described for the primary outcome. Time to death and rehospitalization after 30 days and 1 year will be analyzed by fitting Cox proportional hazards regression models with trial arm as explanatory variable. Hazard ratios including their confidence intervals will be reported. Patients will be censored on their last known follow-up. To illustrate the course of deaths and re-hospitalizations in the two treatment arms, a Kaplan-Meier Curve will be presented.

Length of hospital stay will be calculated in days considering index and each rehospitalization separately and by the sum of all hospital stays. Standard summary statistics for numerical data will be performed. If distribution of data allows, significant differences of mean of length of hospital stay between arms will be assessed with a *t*-test (two-sided α = 5%). If distribution is skewed, data will be transformed or other models selected.

The secondary outcomes (falls, fractures, course of hyponatremia, recurrence of hyponatremia, severe symptomatic hyponatremia, overcorrection of hyponatremia) will be analyzed as described for the primary outcome. To account for multiple occurrences of falls, fractures, and recurrence of hyponatremia after 1 year, we will apply a Poisson model.

Diagnostic performance of biomarkers will be assessed by calculating sensitivity, specificity and accuracy as well as best cut-offs. Gold standard is the correct diagnosis of etiology of hyponatremia, which is expert opinion based on biochemistry results and treatment response.

Analyses of differences of quality of life score and of executive functioning score between arms will be performed also considering grade of hyponatremia and its correction. Multivariate linear models will be used to explore possible associations.

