Even though randomized controlled trials are considered the best study design to assess causality, some limitations of our trial should be mentioned. First, this trial takes place in a real-world setting, so logistical obstacles and reduced adherence to recommended treatment may occur. Non-compliance by both the treating physician and/or the patient may compromise the number of patients in the per protocol analysis. Also, full hyponatremia correction may not be achieved in patients who are quickly discharged. More specifically, we take into account that both premature discharge and non-compliance will affect the number of patients in which full hyponatremia correction can be realized. As a consequence, in a number of patients plasma sodium concentration is expected to increase but not reach normal levels within the hospitalization period. Early discharge can especially limit the chance of successful hyponatremia correction in patients who require treatment escalation or sequential use of various treatment options. Yet, results from this trial will be a good reflection of everyday clinical practice. Second, we anticipate that this trial may increase the overall awareness for hyponatremia in the study centers which may lead to improved hyponatremia management in the control group. However, the problem of contamination is not expected to be significant enough to warrant a cluster-randomization design. Also, cluster-randomization designs are much more susceptible to selection bias and therefore do not outweigh the advantages of individual randomization (60). Third, to avoid contamination, the study team will not order diagnostic tests in the control group. As a result, the etiology of hyponatremia in the control group will be derived from the combination of all available clinical and laboratory findings and treatment response. Follow-up plasma sodium measurements in the control group will be recommended because this is necessary to ensure the planned outcome assessment. We acknowledge that this creates an area of tension between possibly contaminating standard of care and complete data collection to address the primary research question.

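### The arm-by-treatment-used subgroup analysis rests on a variable set after randomisation, by a different process in each arm, so its results are not randomised comparisons and can mislead

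*Protocol article*

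**What the plan says.** All references are to the protocol article.

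- **Subgroup Analyses.** The section asks whether the difference between arms on the primary outcome and its components varies with sex, age, severity of hyponatremia and underlying disease (SIAD is one of seven conditions listed), "as well as the main treatment used (fluid restriction, diuretics, infusion, urea, vaptans". The method is logistic regression with arm, subgroup and their interaction, tested at 5%. The reporting rule is: "If a significant interaction effect results, the treatment effect will be calculated for the respective outcome and subgroups separately".
- **Randomization.** Patients are allocated directly after inclusion.
- **A. Intervention Group (Treatment).** The study team recommends a treatment and reviews it daily. If sodium rises by less than 2 mmol/l in 24 hours, treatment is stepped up or changed to another type.
- **B. Control Group (Treatment).** The attending physicians alone decide on treatment of hyponatremia.
- **Diagnosis of aetiology.** In the intervention arm the initial diagnosis is revised in light of treatment response and made final before discharge. For controls, "The final hyponatremia diagnosis will be made by the study team at discharge", again using treatment response. Their laboratory work-up is left to the attending physician, and the Discussion adds that "to avoid contamination, the study team will not order diagnostic tests in the control group".
- **Secondary Analysis.** Analyses of quality-of-life and executive-functioning differences "between arms will be performed also considering grade of hyponatremia and its correction", with linear models to explore associations.

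**The concern.** A subgroup analysis of a randomised trial is protected by randomisation only if the subgroup is fixed before allocation or cannot be affected by it. Main treatment used fails on both counts. It is decided after allocation, by a different process in each arm, and the choice of treatment is what the intervention changes.

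In the intervention arm, ending up on a later-step treatment partly records failure to respond to an earlier one. In the control arm, the same category records a physician's judgement of that patient. Comparing arms within the category compares differently selected patients.

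What is at stake is a claim about a drug class. An apparent benefit or harm of urea, a vaptan or fluid restriction on death or rehospitalisation would carry the authority of a large randomised trial, although no drug class was randomised.

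**Working it through.** **Step 1: the plan's own figure.** Inputs from Determination of Sample Size: "We set 80% power for a two- sided test with an α error of 5" per cent; "We therefore propose a combined event rate of 23% under standard care"; and "we expect to achieve an absolute risk reduction for mortality and rehospitalization of 5" percentage points. The comparison is therefore 23% against 18%, with mean 20.5%.

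n per arm = [1.960 × √(2 × 0.205 × 0.795) + 0.842 × √(0.23 × 0.77 + 0.18 × 0.82)]² / 0.05² = 1,023, or 2,046 in total. The plan states 2,050 evaluable. 2,050 / 0.9 = 2,278, as stated. Power at 1,025 per arm is 80.1%. The sample size reproduces, and nothing below changes it.

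**Step 2: the sections side by side.**

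| Question | Intervention arm | Control arm |
|---|---|---|
| When is main treatment set? | After allocation | After allocation |
| Who sets it? | Study team recommends | Attending physician |
| What changes it? | Stated rule on sodium response | Physician's discretion |
| Can a patient fit none of the five categories? | If the recommendation is not carried out | Yes, if none of the five is given |

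The Discussion gives reasons to expect selection. It offers more active treatment of severe hyponatremia as one possible explanation of mortality patterns, and it says early discharge limits patients who need escalation or several treatments in sequence.

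**Step 3: can selection alone produce a subgroup effect?** The documents give no data on who receives which treatment, so every input here is an assumption. Suppose the arm has no effect on anyone. Half the patients have low risk and half high risk, with mean 23%. Treatment is reduced to two categories, escalated or not, and the probability of escalation, p, depends on risk group and arm. Within an arm:

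risk among escalated = (p_low × r_low + p_high × r_high) / (p_low + p_high)

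Worked example: r = 13% and 33%; control p = 5% and 25%; intervention p = 40% in both groups.

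- Control: (0.05 × 0.13 + 0.25 × 0.33) / 0.30 = 29.7%.
- Intervention: (0.40 × 0.13 + 0.40 × 0.33) / 0.80 = 23.0%.
- False difference: -6.7 points.

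The last two columns give the false risk difference among escalated patients, in points, and in brackets the rejection rate of a nominal 5% interaction test (20,000 simulated trials, 1,025 per arm).

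| Control p (low, high) | Intervention p (low, high) | Risks 18%/28% | Risks 13%/33% |
|---|---|---|---|
| 5%, 5% | 20%, 40% | +1.7 (4.7%) | +3.3 (8.2%) |
| 2%, 10% | 40%, 40% | -3.3 (9.9%) | -6.7 (22.2%) |
| 5%, 20% | 35%, 45% | -2.4 (8.1%) | -4.8 (16.8%) |
| 5%, 25% | 40%, 40% | -3.3 (14.1%) | -6.7 (39.0%) |
| 10%, 10% | 10%, 10% | 0 (4.5%) | 0 (4.9%) |

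The sign depends on how selection differs between arms. The bias vanishes when treatment choice depends on neither arm nor risk (last row). The table shows that the artefact can exceed the planned 5 points; it does not predict its size in this trial.

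**The case against.** The best defence is that this is one exploratory analysis. The section is worded as a matter of interest and makes no confirmatory claim. The primary χ²-test, the separate component analyses, the Cox models and the sample size do not depend on it. That stands, and it limits how serious the point is. It does not rescue the analysis: the section puts main treatment beside sex and age and promises treatment effects within its categories. An unseen analysis plan could refine the definition, but any definition by the treatment actually used after allocation has the same defect.

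A reader might infer more than the documents support:

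- **That the results will mislead, or show a large harm.** Neither size nor direction can be derived from the documents. That some controls receive none of the five treatments is plausible but not stated.
- **That the aetiology subgroups are defined at discharge.** Subgroup Analyses does not say which diagnosis defines SIAD, and an initial diagnosis exists in the intervention arm. The discharge diagnosis is the only study-team diagnosis described for controls, so the inference is reasonable, but it remains an inference. The other six conditions are mostly present before randomisation.
- **That controls have no diagnostic tests.** Only the study team refrains from ordering them; attending physicians may test. Work-up may differ between arms but is not absent.
- **That the quality-of-life and executive-function comparisons adjust the effect away.** The wording allows an unadjusted arm difference as well, and the models are described as exploring associations. Conditioning on correction would remove the part of the effect that passes through it and may add bias, but the plan does not say this is the only result.
- **That the number of tests is itself the fault.** Over three outcomes it is 15, 33 or 45 depending on coding (5, 11 or 15 tests each), or 0.75, 1.65 or 2.25 expected false positives at 5%. This, and showing effects only after a significant interaction, would concern sex and age equally. It is a separate matter of preference.

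**Conclusion.** The point holds for main treatment used, and there it rests on stated text. The plan fits an arm interaction with a variable that follows randomisation, arises differently in each arm and belongs to the intervention. The resulting contrasts are not randomised and can mislead in either direction. The range of +3.3 to -6.7 points, with rejection in about 5% to 39% of trials, rests wholly on the assumed inputs above.

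For SIAD the point is conditional on use of the discharge diagnosis. For quality of life and executive function it is a matter of which result leads and how the other is labelled.

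The plan should be changed on this point, but the fault does not threaten the trial's main conclusion. The primary analysis, the sample size, and the subgroups by sex, age and presenting severity are not affected.

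**What to change.** 1. Remove main treatment used from the between-arm subgroup list and describe the treatments given in each arm, with a category for patients who received none of the five. If the analysis is kept, label it non-randomised wherever it is reported.
2. State which diagnosis defines the SIAD subgroup. If it is the discharge diagnosis, define SIAD instead from information available before randomisation in both arms.
3. For quality of life and executive functioning, give the arm difference without adjustment for sodium correction as the main result. Label models that include correction as non-randomised associations.

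The cost is a change of wording before the data are analysed and the loss of one exploratory subgroup. No patient numbers or stated figures change.

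### Subgroup interactions are tested at an unadjusted 5% on three outcomes, and subgroup effects are promised only after a significant test, so the promised estimates are exaggerated by selection

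*Protocol article*

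**What the plan says.** All of this stands under Subgroup Analyses in the protocol article.

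- **Outcomes.** The question is whether the treatment effect "on the primary outcome and its components varies between the following patient subgroups". That is three outcomes: the composite, death and rehospitalization.
- **Two-level factors.** "sex (female and male), age (<70 and ≥ 70 years), severity of hyponatremia", the last split at 120 mmol/l.
- **Multi-category factors.** "underlying disease (stroke, heart failure, SIAD, hepatic impairment, chronic kidney disease, malignancy, surgical diagnosis") and "main treatment used (fluid restriction, diuretics, infusion, urea, vaptans"). The section does not say whether each list is one factor or a set of yes/no factors.
- **Model.** "we will fit logistic regression models, including treatment arm, subgroup and the interaction term as explanatory variables".
- **Threshold and consequence.** The rule reads: "Significance for interaction is defined by α = 5%. If a significant interaction effect results, the treatment effect will be calculated for the respective outcome and". The sentence ends by applying this to each subgroup in turn.

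The section contains no multiplicity adjustment, no exploratory label, and no commitment to subgroup estimates when the interaction is not significant.

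**The concern.** This is an operative rule, so a later analysis plan would have to override it, not merely complete it. It has two weaknesses.

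The first is the number of tests. Each is called significant at 5%, and there are at least 15. Without any real effect modification, a falsely significant interaction is a common result of the procedure.

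The second does not depend on the count. The trial is sized for its main effect and has little power for interactions. An interaction that reaches 5% must look large, so subgroup effects calculated on that condition are too far apart on average. If the true effect is the same in everyone, the rule tends to show an inflated benefit on one side and almost none on the other. The risk is mistaken targeting of treatment by sex, age, severity or diagnosis, under a rule that looks prespecified and formal.

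**Working it through.** **Inputs from the protocol article.** Determination of Sample Size gives a composite rate of 23% under standard care, a 5-point absolute reduction (so 18%), death 6.4%, rehospitalization 18.5%, 2,050 evaluable patients, and a two-sided 5% test with 80% power. Allocation is 1:1 (Randomization). The 5% interaction level, the factors and the three outcomes come from Subgroup Analyses.

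**Assumptions.** Subgroup prevalences are not given; values between 5% and 55% were used. The overlap of death and rehospitalization is taken as 2 points of all patients, since 6.4 + 18.5 - 2 = 22.9, which matches the stated 23%. There is no true interaction unless stated.

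**1. The plan's own figure.** Per arm, n = [1.960 × √(2 × 0.205 × 0.795) + 0.842 × √(0.23 × 0.77 + 0.18 × 0.82)]² / 0.05² = (1.119 + 0.480)² / 0.0025, or about 1,023. The total is 2,046 against the stated 2,050, and 2,050 / 0.9 = 2,278. The sample size reproduces; power at 1,025 per arm is 80.1%.

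**2. Chance of at least one false interaction.** For k independent tests it is 1 - 0.95^k. The tests are not independent (composite and rehospitalization correlate at about 0.88), so trials of 2,050 patients were simulated with the three outcomes drawn jointly.

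| Coding | Tests | If independent | Simulated, three outcomes | Simulated, primary outcome only |
|---|---|---|---|---|
| Five factors | 15 | 53.7% | about 45% (all two-level) to 48% (disease and treatment multi-level) | 22-23% |
| Ten baseline yes/no factors (seven diseases separate, main treatment left out) | 30 | 78.5% | about 67-72% | about 39-40% |
| Eleven factors (seven diseases separate, main treatment as one) | 33 | 81.6% | about 76% | about 44% |

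The expected number of false positives over the three outcomes is about 0.8 with five factors and 1.8 with eleven.

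**3. Power for an interaction.** In a 50/50 subgroup each half has 512.5 patients per arm. The SE of the interaction log odds ratio is √[(2/512.5) × (1/(0.23 × 0.77) + 1/(0.18 × 0.82))] = 0.220. Significance therefore needs a ratio of odds ratios of at least exp(1.96 × 0.220) = 1.54. If the true interaction is as large as the whole planned effect (log OR 0.308), then z = 0.308 / 0.220 = 1.40, power is about 29%, and significant estimates are about 1.8 times too large. If it is half that size, power is about 11% and the factor is about 3.5.

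**4. Selection when the effect is the same in both halves (-5 points).**
- SE of the risk difference in one half: √[(0.23 × 0.77 + 0.18 × 0.82) / 512.5] = 2.52 points. SD of the difference between halves: 2.52 × √2 = 3.56 points.
- No condition: the mean absolute gap is 0.798 × 3.56 = 2.84 points. The better and worse halves average -5 ∓ 1.42, that is -6.4 and -3.6.
- Given interaction p < 0.05: the mean |z| is 2 × 0.0584 / 0.05 = 2.34, so the mean gap is 2.34 × 3.56 = 8.32 points. The halves average -5 ∓ 4.16, that is -9.2 and -0.8.
- Direct simulation gives -9.1 and -0.8 to -0.9. In about 30-31% of these selected cases the worse half lies above zero.

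**The case against.** Several parts of the case for the plan stand.

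- **The procedure is better than many.** The factors are named in advance, and a formal interaction test precedes any subgroup estimate. The single primary test keeps its 5% type I error.
- **A false subgroup finding is not shown to be more likely than not.** A reader might infer this from the number of tests. It holds only if the seven diseases are tested separately. That is plausible, because they can coexist in one patient and no rule assigns each patient to one, but the text does not state it. With five factors the chance is a little under one half.
- **The text does not bar other displays.** A reader might also infer that consistent subgroups will never be shown. The section says what happens after a significant interaction and is silent otherwise; a forest plot of all subgroups is not excluded. What stands is that the only estimates it commits to are the selected ones.
- **The apparent-harm figure needs its base rate.** The 30-31% is conditional on an event of about 5%, so a significant interaction with a half above zero occurs in about 1.5% of trials per factor (0.05 × 0.31). Showing every subgroup would display a half above zero more often, in about 4%. Full display removes the selection bias; it does not remove chance findings.
- **Multiplicity policy is often left to the analysis plan**, which is not shown and may call these analyses exploratory. That limits the weight of the point. It does not remove it, because the article itself fixes the 5% threshold and its consequence.

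**Conclusion.** The point holds as a defect of interpretation and reporting. With no true interaction, the stated rule yields at least one falsely significant interaction in roughly 45-48% of trials for five factors on three outcomes, about 23% on the primary outcome alone, and about 67-76% if the diseases are separate factors. These figures rest on assumed prevalences and on the planned event rates.

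The exaggeration is the firmer part, because it does not depend on how the factors are counted: about -9 and -1 points after a significant interaction, when the truth is -5 in both halves of a 50/50 subgroup. About 1.4 points of the shift on each side come merely from labelling the halves better and worse afterwards; the condition on significance adds about 2.7 more (4.16 - 1.42).

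The documents do not support a claim that the primary conclusion is at risk, or that the plan forbids reporting the other subgroups.

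**What to change.** Replace the last two sentences of Subgroup Analyses with wording to this effect: the treatment effect with its 95% CI will be calculated and reported for every prespecified subgroup and outcome, whatever the interaction p-value; interaction p-values will be reported as exploratory, together with the number of tests done; no confirmatory subgroup claim will be made from an unadjusted p-value. Stating the number of tests also requires saying whether the diseases and treatments are single factors or separate yes/no factors.

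The cost is one wording change and a forest plot per outcome, with no new data or patients.

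Holm adjustment is optional. With five factors its first step is 0.05 / 5 = 0.01, and power for an interaction as large as the planned effect would fall from about 29% to about 12% (P[Z > 2.576 - 1.40]). That is a trade-off for the sponsor to weigh and is not needed to remove the selection.
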